## Methods

### Study Design and Objectives

The objective of this study is to evaluate the impact of having access to the Purrble intervention, compared with an active control in the form of a noninteractive plush toy, on child daily ER (primary outcome) as well as a range of secondary outcomes over 1 month.

The study is a 2-arm, exploratory randomized controlled trial comparing an intervention group (Purrble) with an active control group (noninteractive plush toy). The deployment period will be 4 weeks and will include daily parent self-report measures via ecological momentary assessment (EMA), as well as weekly validated surveys with a 1-month and 6-month follow-up (see Figure 1). The intervention period will start immediately after children receive their arm-appropriate toys. Participants in both the intervention and active control groups (Figure 2) will be able to keep the toys after the deployment period ends. Active control group participants will not be offered Purrble units postdeployment, as this would unblind the conditions before follow-up data collection.

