### Outcome Measures

The primary outcome will be a daily EMA measure of child emotion regulation capability (as reported by parents) over a period of 4 weeks. Exploratory analyses will investigate the intervention impact on secondary outcomes of child emotion regulation, collected weekly over the same 4-week period, with follow-ups at 1 month and 6 months postdeployment. See Table 1 for a summary of the outcome measures and assessment times.

**Table 1 table1:** Summary of the outcome measures and assessment times.

Outcome measure	Baseline	Deployment				Follow-up			
		Week 1	Week 2	Week 3	Week 4	1 week	2 weeks	1 month	6 months
Perceived child ER ability		Collected daily	Collected daily	Collected daily	Collected daily				
Daily parent report ecological momentary assessment (modified differential emotions scale)		Collected daily	Collected daily	Collected daily	Collected daily				
Daily parent report ecological momentary assessment (engagement)		Collected daily	Collected daily	Collected daily	Collected daily				
Daily parent report ecological momentary assessment (reaction to triggers)		Collected daily	Collected daily	Collected daily	Collected daily				
Weekly parent questionnaire (Strength and Difficulties Questionnaire)	✓	✓	✓	✓	✓			✓	✓
Weekly parent questionnaire (ER Checklist)	✓	✓	✓	✓	✓			✓	✓
Weekly parent questionnaire (Twente Engagement With eHealth Technologies Scale)		✓	✓	✓	✓			✓	✓
Weekly children questionnaire (Difficulties in ER Scale)	✓	✓	✓	✓	✓			✓	✓
Weekly children questionnaire (emotion regulation-beliefs)	✓	✓	✓	✓	✓			✓	✓
Interviews with families						✓	✓		

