#### Primary Outcome Measure

The primary outcome measure will consist of a composite end-of-day 4-item parent report measure of the *perceived child ER* ability throughout the day. The specific items are listed below, all measured as a visual analog scale [62,63] with *not at all* and *very much so* as the anchors. The composite score for each day will be computed as the mean value across the 4 items:

Today, to what extent was your child able to take difficult things in a stride?Today, to what extent did your child get easily triggered or upset? (reverse-scored)Today, to what extent was your child able to calm down easily if upset?Today, to what extent did your child get very emotional even after the littlest things? (reverse-scored)

Specifically, this EMA item composite aims to indirectly tap into day-to-day changes in a child’s ability to downregulate their emotions after (and thus cope with) triggering situations they routinely experience in their daily life. Our expectation is that contact with the Purrble will lead to the following:

Lower intensity negative emotions after facing everyday stressors (eg, by being able to downregulate before emotional response escalate—cf, level 1 in the theory of change).Briefer duration of negative emotions after facing everyday stressors (eg, being able to downregulate emotions faster with Purrble—cf, levels 1 and 3 in the theory of change).

By being measured repeatedly over time and within subjects, the items capture the changes in emotional outcomes that would indicate changes in the child’s ER ability, assuming that the trait-based reactivity to daily stressors remains stable. The items were thus selected to tap into the proximal outcomes of ER behavior that (1) would be affected if the intervention is effective, (2) is directly observable by parents, (3) is state-based (rather than trait-based) to enable daily measurement, and (4) is connected to the intervention theory of change.

The item selection drew on a range of established measures of emotion dysregulation (Strengths and Difficulties Questionnaire, SDQ [64], Emotion Regulation Checklist, ERC [65], Difficulties in Emotion Regulation Scale (DERS) [66], and Children’s Emotional Management Scales [67]), as well as qualitative data from previous deployments [31,32] with parental reports of increased emotion regulation after potentially triggering events being the common theme.

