##### Weekly Parent Reports

We will also collect *secondary distal outcomes* for both the intervention and active control groups, with 5 data points collected during the 4-week main deployment period: at baseline (just before intervention or control toys are delivered), and then weekly for a period of 1 month (end of week 1, week 2, week 3, and week 4), and then at 1-month and 6-month follow-up. The measures include parent reports on distal outcomes of child emotion regulation (SDQ and ERC) and engagement (adapted Twente Engagement With eHealth Technologies Scale [TWEETS]), as well as child reports on their emotion regulation strategies (DERS) and emotion regulation beliefs (ER mindset).

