#### Hypotheses

##### Primary Hypothesis

Across the trial, we hypothesize that access to the Purrble intervention (as opposed to the active control) will lead to an *increase in parent-reported daily child ER ability*, as measured by the primary outcome.

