#### Data Analyses

All analyses of daily EMA outcomes (the primary outcome of daily ER and secondary outcomes of engagement with the toy and mood), as well as the analyses of the weekly outcomes, will be conducted using random-effect models for longitudinal regression. These models consider the nested nature of repeated-measures data and are robust to data missingness and violations of the normality assumption. The regression models will examine the difference in the outcome as a function of the assigned condition (Purrble vs active control). The models will adjust for the baseline levels of the score on the total difficulty scale in the SDQ to decrease noise. To account for participant-to-participant variability in EMA scoring as well as in trajectories of change in EMA scores over time, we will include a random intercept and random slope for time. All analyses will be conducted on an intent-to-treat basis and will use data from all randomized participants regardless of their level of participation.

A separate model will be fitted to each outcome. Given that this is an exploratory trial, we will not formally adjust for multiple comparisons. However, we will be cautious in our conclusions about any significant findings and will interpret all results in light of all performed analyses.

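### The primary daily score has no pre-toy value, so change from before the toy cannot be estimated on it and avoidable precision is lost; the randomised comparison stays valid

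*Protocol article*

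**What the plan says.** The Outcome Measures section defines the endpoint: "The primary outcome will be a daily EMA measure of child emotion regulation capability (as reported by parents) over a period of 4 weeks". In Table 1 the row "Perceived child ER ability" has an empty Baseline cell and daily entries for weeks 1 to 4. Study Design and Objectives fixes the start of that period: "The intervention period will start immediately after children receive their arm-appropriate toys".

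The weekly measures are treated differently. Weekly Parent Reports schedules them "at baseline (just before intervention or control toys are delivered), and then weekly for a period of 1 month", and Table 1 ticks Baseline for the SDQ, the ERC, the DERS and the ER beliefs questionnaire.

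Data Analyses names one baseline covariate: "The models will adjust for the baseline levels of the score on the total difficulty scale in the SDQ to decrease noise". It also specifies a random intercept and a random slope for time. The Primary Hypothesis is an "increase in parent-reported daily child ER ability" with Purrble as opposed to the control toy, and the rationale under Primary Outcome Measure is: "By being measured repeatedly over time and within subjects, the items capture the changes in emotional outcomes".

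**The concern.** All the scheduled ER questionnaires have a pre-toy value, but the primary ER score does not. Two things follow.

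- **Interpretation.** The within-child data show change during toy use, not change from before it. Level 1 of the logic model is in-the-moment soothing, so an early effect may already be inside the first reading, where a slope over the four weeks cannot show it.
- **Precision.** The plan assumes a daily rating that is highly stable within a family (correlation 0.75). With such a rating, most of the variance of a 28-day mean is the family's own level. A pre-toy reading of the same items would remove much of it. The SDQ is a different scale, and its range is restricted by the entry rule of 10 points or more, so it can be expected to remove less.

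**Working it through.** **Inputs.** From Sample Size and Power: d = 0.3, α = .05 (taken as two-sided), 90% power, correlation ρ = 0.75, required N = 92, final N = 120. From Outcome Measures: 4 weeks, so m = 28 daily scores. From the Abstract: 1:1 allocation. Assumption: all days are equally correlated, and the contrast is the difference in 28-day means. This stands in for the condition effect in the mixed model.

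**Formulas**, in units of the single-day variance:
- No pre-toy report: V = (1 + 27ρ)/28.
- With b pre-toy reports as covariate: subtract ρ² / [(1 + (b − 1)ρ)/b].
- SE = √(4V/N); power = Φ(0.3/SE − 1.96); n per arm = 2(1.960 + 1.282)²/0.3² × V = 233.5 × V.

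**Variance at ρ = 0.75**
- None: (1 + 20.25)/28 = 0.759.
- One: 0.7589 − 0.5625 = 0.196, a cut of 74%.
- Five: 0.7589 − 0.5625/0.8 = 0.056, a cut of 93%.

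**The plan's own figure.** With one pre-toy report, 233.5 × 0.1964 = 45.9, so 46 per arm and 92 in all, which is the stated number. With none, 233.5 × 0.7589 = 177.2, so 178 per arm and 356 in all. The match with 92 is not proof of what was done. A post-only repeated-measures calculation with 0.3 entered as Cohen f (equal to d = 0.6) also gives 92.

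**Power before SDQ adjustment**

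| Families | No pre-toy report | One |
|---|---|---|
| 92 | SE 0.182, 38% | SE 0.092, 90% |
| 120 | SE 0.159, 47% | SE 0.081, 96% |

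**With SDQ adjustment.** The correlation s of baseline SDQ with a single day's score is not given, so it is assumed, and taken as equal for pre-toy and post-toy days. V with SDQ alone = 0.7589 − s². One pre-toy report then removes a further (0.75 − s²)²/(1 − s²).

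| s | V, SDQ only | Power at 92 / 120 | V, SDQ + one report | Further cut | Power at 120 |
|---|---|---|---|---|---|
| 0.3 | 0.669 | 42% / 52% | 0.190 | 72% | 96% |
| 0.5 | 0.509 | 52% / 63% | 0.176 | 66% | 98% |
| 0.7 | 0.269 | 79% / 89% | 0.136 | 49% | 99% |

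**Lower correlation.** At ρ = 0.5 without SDQ, V is 0.518, 0.268 and 0.101 with none, one and five reports (cuts of 48% and 80%). Power at 92 is 52%, 79% and above 99%.

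**Correlation that fades over days.** Assume each day's score is a stable family level, plus an AR(1) part (0.8 to 0.9 per day), plus noise. The share of variance removed is cov(pre mean, post mean)² / [var(pre mean) × var(post mean)]. With a stable share of 0.3 to 0.5 and noise of 0.1 to 0.3, five reports immediately before the toy remove 36% to 69%. With a stable share of only 0.1 and noise of 0.25 to 0.5, they remove 15% to 24%.

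**The case against.** The strongest reply is that nothing is invalid here. The primary question is a randomised between-arm difference, which is unbiased without a baseline and has a controlled error rate. The sentence in Primary Outcome Measure sits in a paragraph about day-to-day change, which the plan does measure and model with a random slope. The trial describes itself as exploratory. All of this stands, and it rules out three stronger readings that a reader might infer.

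- *That the trial cannot measure the change it sets out to capture.* It can measure change during the four weeks and the difference between arms. Only change from a pre-toy level is out of reach on this measure.
- *That a chance difference between arms in parents' rating level could pass for a toy effect.* At 120 families that imbalance has SD √(4 × 0.75/120) = 0.158, almost the same quantity as the standard error of 0.159. It is ordinary sampling error, already counted in the test.
- *That a pre-toy level would by itself tell whether both toys helped or neither did.* There is no arm without a toy, and children are selected on SDQ of 10 or more, so regression to the mean would remain. The SDQ, ERC, DERS and beliefs measures already give some descriptive before-and-after information.

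It is also fair to say that the 38% and 47% power figures leave out the SDQ covariate, and that 38% uses 92 families although all randomised families are to be analysed. The SDQ table above answers this: the gain shrinks but does not vanish. Finally, the Results section reports that primary data collection was finished by mid-May 2021, so a change of schedule may come too late for this trial.

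**Conclusion.** The point holds as one of precision and wording. The primary score has no pre-toy value, and the model adjusts only for the SDQ. Change from before the toy is therefore not estimable on the primary measure, and a cheap gain in precision is passed over. At the plan's own ρ = 0.75 the loss is large: 74% of the variance for want of one report and 93% for want of five, before SDQ adjustment. With an SDQ correlation of 0.3 to 0.7, one report still removes 72% to 49% of what remains. With fading correlation, five reports remove roughly one third to two thirds, and less if the stable share is very small.

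These sizes rest on assumed correlation structures and on the 28-day mean as the contrast. Figure 1, the assessment design, is not shown, so the timing rests on Table 1 and the text, which agree. A reader might also infer that the sample size counted on a baseline that is not collected. The documents do not settle that, because 92 can be reached in other ways.

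**What to change.** 1. Add the four primary items, and the mDES mood items, to the baseline survey that parents complete before randomisation. Fill the Baseline cell in Table 1. The items ask about today, so have them answered at the end of the day, as later.
2. Enter the pre-toy score as a covariate in the primary model, alongside baseline SDQ.
3. Optionally, collect a few daily reports just before toy delivery. This protects the gain if correlation fades between the survey and the toy. At ρ = 0.75, five pre-toy plus 23 post-toy days give V = (1 + 22 × 0.75)/23 − 0.5625/0.8 = 0.058, against 0.056 with all 28 post-toy days, so total burden need not rise.
4. Unless a pre-toy value is collected, reword the rationale under Primary Outcome Measure to say that the items capture change during toy use.

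**Cost.** Steps 1 and 2 add a handful of visual analog items to an existing survey and one model term, with no extra staff. Step 3 costs a little more burden or a slightly shorter post-toy series, plus reminders timed to delivery. If collection is already complete, step 4 remains, with a note in the report that no pre-toy level exists, and steps 1 to 3 pass to the follow-on studies foreseen under Limitations.

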#### Secondary Outcome Measures

##### Daily Parent Report EMA

In addition to the primary EMA outcome, we will collect several other daily EMA parent reports. The psychological constructs targeted are the *child’*s *general mood* and *daily engagement with the toy.*

The *child’s daily mood* is measured by selected Modified Differential Emotions Scale (mDES) [68] emotion triplets, balancing 2 negative and 2 positive sets, while being informed by previous qualitative studies. The items are listed as follows, all measured on a visual analog scale [62,63], with *not at all* and *extremely* as the anchors:

How stressed, nervous, or oevrwhelmed did your child feel today?How joyful, glad, or happy did your child feel today?How angry, irritated, or annoyed did your child feel today?How proud, confident, or self-assured did your child feel today?

The *daily engagement item* asks about the general perception of engagement with the toy (*How much did your child play with the toy today?*)*,* measured on a visual analog scale [62,63], with *not even once* and *they were inseparable* as the anchors.

Finally, we will include a *series of explorative items that examine the child’s reaction after potentially triggering events*. We will first ask the parents *Did anything happen today that would typically upset your child?* If yes, the protocol follows with several questions collecting qualitative and quantitative information regarding the number of such situations, the intensity and length of subsequent children’s negative reactions, how many of these situations the child used the toy, who initiated the use, how helpful or unhelpful it was, and an opportunity to share open-ended comments or observations. The purpose of these items is to gain a qualitative understanding of the toys’ use in challenging situations and to guide post deployment interviews.

##### Weekly Parent Reports

We will also collect *secondary distal outcomes* for both the intervention and active control groups, with 5 data points collected during the 4-week main deployment period: at baseline (just before intervention or control toys are delivered), and then weekly for a period of 1 month (end of week 1, week 2, week 3, and week 4), and then at 1-month and 6-month follow-up. The measures include parent reports on distal outcomes of child emotion regulation (SDQ and ERC) and engagement (adapted Twente Engagement With eHealth Technologies Scale [TWEETS]), as well as child reports on their emotion regulation strategies (DERS) and emotion regulation beliefs (ER mindset).

**Weekly Questionnaires—Parents**

*Parent-reported emotional and behavioral difficulties of the child* will be measured using the 25-item SDQ [64]. This well-established measure has shown satisfactory reliability and validity [64,69] and is commonly used to measure the impact of child-orientated interventions [46,47].

*Parent-reported ER lability and competence* will be measured using the 24-item Emotion Regulation Checklist [65] questionnaire. The ERC measures children’s general emotion regulation capacities and consists of 23 questions divided into 2 subscales, which we will consider separately: the Lability or Negativity subscale measures inflexibility, liability, and dysregulation, whereas the Emotion Regulation subscale measures positive emotion regulation behavior and capacities, appropriate emotional expression, empathy, and emotional self-awareness. ERC is one of the most commonly used measures of emotion regulation in children [5].

The *parent-reported behavioral, cognitive, and affective engagement* with the intervention will be measured using an adapted version of the Twente Engagement with E-health Technologies Scale (TWEETS) [70] questionnaire. TWEETS is a new, promising instrument specifically designed to measure engagement with digital mental health interventions, with good reliability in previous studies [70]. The adaptation here is necessary to track parents’ perceptions of child engagement, rather than the original self-report version. See Multimedia Appendix 1 for the fully adapted instrument.

**Weekly Questionnaires—Children**

*Child-reported emotion dysregulation* will be measured by a shortened version of the brief DERS [71], following previous work with children of similar ages (8-9 years [72]). DERS has been developed to measure clinically relevant difficulties in ER across 6-factor analytically derived subscales (awareness of emotion, clarity about own emotions, nonacceptance of emotion, lack of effective emotion regulatory strategies, lack of ability to engage in goal-directed activities, and lack of ability to manage impulses). The DERS [71,73] has been used extensively to facilitate understanding of how emotion dysregulation is associated with psychiatric symptoms and to measure treatment progress. See Multimedia Appendix 1 for the full adapted instrument.

Child-reported *beliefs about ER* beliefs questionnaire [54] have been adapted to child populations. The questionnaire measures child *entity beliefs* about their emotions [52,55,74], that is, whether children believe their emotions to be controllable. To simplify the required cognitive load, the adapted measure asks children to pick 1 out of 4 statements (eg, *I cannot control my feelings at all, I can control my feelings a little, I can control my feelings a lot,* and *I can control my feelings all the time*) rather than using the original Likert scale statements asking about agreement (eg, *The truth is, I have very little control over my emotions*). Our preliminary validation (221 children, aged 6-10 years, US sample) showed good reliability (0.844) (internal pilot study), compared with the adult version [54]. See Multimedia Appendix 1 for the full adapted instrument.

#### Postdeployment Interviews (Process Analysis)

We will collect semistructured interview data with parents of up to 40% of the experimental group sample (20-25 families), and approximately 25% of the control group (15 families). The interviews will be conducted within 2 weeks following the primary data collection period. We will specifically aim to recruit families who show the highest or lowest change in the outcome data over the primary period to qualitatively understand the potential moderators of intervention responses for future research.

Following previous work [31], the semistructured interview guide will explore the engagement with the toy, any qualitative changes in child or family behavioral patterns that parents notice, appropriation (ie, how the intervention ended up being used by different participants), and use trajectory over time. In addition, we draw on the data from daily questionnaires as part of the interviews, such as discussing the trajectories of daily parental reports on child ER with the parent (eg, asking about specific instances where there is a spike or as a way of referring to particular times in the deployment).

#### Hypotheses

##### Primary Hypothesis

Across the trial, we hypothesize that access to the Purrble intervention (as opposed to the active control) will lead to an *increase in parent-reported daily child ER ability*, as measured by the primary outcome.

##### Secondary Hypotheses

Intervention effects will be moderated by daily engagement with toy and weekly data from the TWEETS questionnaire. In addition, we expect to see between-group differences in favor of Purrble for the secondary daily EMA parental-report outcomes: *an increase* in the *positive mDES items* and a *decrease* in the *negative mDES items*.

Finally, as exploratory analyses, we will investigate the following hypotheses for weekly outcome measures:

The decrease in *parent-reported emotional and behavioral difficulties* (as measured by the SDQ) will be greater in the intervention group (smart toy) than in the active control group (noninteractive toy).*The decrease in ER lability* and *increase in emotion regulation competence* (as measured by the Lability or Negativity subscale and Emotion Regulation subscale questionnaires respectively) will be greater in the intervention group than in the active control group (noninteractive toy).*Behavioral, cognitive, and affective engagement* with the intervention, as measured by the adapted *TWEETS questionnaire for parents*, will be higher for the intervention than the control group.The decrease in *child-reported emotion dysregulation* (as measured by the DERS) will be greater in the intervention group than in the active control group (noninteractive toy).The decrease in *child-reported entity beliefs of emotion regulation* (as measured by the ER mindset questionnaire) will be greater in the intervention group than in the active control group (noninteractive toy).

